**FIGURE 1 eph13343-fig-0001:**
[figure not shown]
Schedule of enrolment, interventions and assessments. Abbreviations: CPM, conditioned pain modulation; EIH, exercise‐induced hypoalgesia; GPAQ, global physical activity questionnaire; NDI, neck disability index; PCS, pain catastrophizing scale; SF‐36, 36‐item short form survey; ‐t_1_, enrolment week 0; t_0_, allocation; t_1–2_, intervention, baseline and post‐intervention assessments; TS, temporal summation; TSK, Tampa scale of kinesiophobia.

This study is a randomized crossover trial, in which all participants will take part in all interventions, but the order in which they are assigned to the interventions is randomized. Participants will attend the first data collection session, during which baseline questionnaires and physical assessments will be measured, followed by the intervention, and a post‐intervention physical assessment will be measured. There will be a 1‐ to 2‐week washout period before the second data collection session, which is identical to the first session minus the baseline questionnaires, with a different intensity of intervention.

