### Procedures

2.4

Participants who meet the inclusion criteria will be invited to attend two testing sessions: one to perform high‐intensity submaximal aerobic bicycle exercise (HIGH); and a second to complete a low‐intensity submaximal aerobic bicycle exercise (LOW). The order of these two testing sessions will be randomized. Participants will be asked to refrain from analgesics on the day of testing and to abstain from physically demanding activities, including exercise, for 48 h before testing. Participants will also be asked to abstain from nicotine, alcohol and caffeine for 12 h before testing.

Participants will be given a detailed explanation about the research study and the requirements of them. Informed consent will be obtained from the participants before collecting any data. Figure 2 depicts the flowchart of study procedure and the assessments conducted at each assessment time point. Participants will be randomized into two main groups, termed the INV‐A group and the INV‐B group, with INV‐A doing HIGH–LOW and INV‐B doing LOW–HIGH. Participants will wait 10 min before commencing the exercise intervention to prevent a carryover effect from the baseline physical assessments influencing exercise. During the waiting time, resting heart rate (HR) and blood pressure will be measured, and appropriate warnings and precautions will be briefed. Participants will then complete the assigned exercise intervention, immediately followed by postexercise assessment. The order of testing will be kept constant within each testing session, both before and after exercise. To prevent a carryover effect, the sessions will be scheduled 1–2 weeks apart.

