### Randomization

2.5

The participants will be enrolled sequentially. After informed consent is obtained, participants will be allocated randomly to one of two groups: INV‐A or INV‐B. Block randomization will be performed with a 1:1 allocation ratio, using the website https://www.sealedenvelope.com/. A table with random numbers generated by the website will be used. Opaque and sealed envelopes containing cards with the name of the intervention group will be used to ensure concealed allocation. A researcher not part of the study will perform the allocation procedure. Owing to the nature of the study trial, blinding of the assessor and participants is not possible.

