### Statistical analysis

2.9

All data will be analysed via scatterplots, boxplots and Kolmogorov–Smirnov statistics to evaluate normality. Normally distributed data will be reported as the means and 95% confidence interval. Other data will be reported as the median and interquartile range. Parametric tests will be used for normally distributed data, and non‐parametric tests for non‐normal distributed data, to analyse between‐group differences for physical outcome measures and baseline questionnaires and physical measures.

To test for carryover effects, the sum of the measured values in the sessions for each patient will be calculated and compared across the two groups with Student's unpaired *t*‐test (Wellek & Blettner, 2012). A *P*‐value of >0.05 indicates no carryover effects, and the ‘washout’ duration is sufficient. To determine the statistical difference between HIGH and LOW, the within‐subject difference in outcome parameters between both sessions will be calculated using Student's unpaired *t*‐test. If there is a statistical significance, a regression model will be conducted to evaluate the effect of exercise intensity (HIGH vs. LOW) on CS measures. The fixed effect of time (baseline and postexercise), exercise intensity and study group will be included in the model, with age as a covariate. If no statistical difference is detected, repeated‐measures ANOVA will be performed to assess significant differences between both groups; the within‐subject factor will be defined as ‘time’, with ‘group’ as a between‐subject factor. The significance level will be adjusted by the number of comparisons using Bonferroni correction.

Multivariate regression analysis will be used to analyse the association between [La] and EIH. In order to examine the relationship between individual measures of CS (EIH, CPM and TS), separate regressions will be conducted. Models will be adjusted for age, sex, education level, physical activity level, NDI, PCS and TSK. Statistical significance is set at *P* < 0.05.

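### A non-significant HIGH-versus-LOW test triggers an ANOVA on the sequence groups, which as written does not compare intensities and has an undefined error rate

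*Protocol article*

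**What the plan says.** The design is a two-session crossover: "all participants will take part in all interventions, but the order in which they are assigned to the interventions is randomized" (section 2.2). Under section 2.5, "participants will be allocated randomly to one of two groups", and section 2.4 defines these groups by order, "with INV‐A doing HIGH–LOW and INV‐B doing LOW–HIGH".

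Section 2.9 first compares participant sums between the two groups as a carryover test. It then turns to the treatment comparison: "To determine the statistical difference between HIGH and LOW, the within‐subject difference in outcome parameters between both sessions will be calculated", using an unpaired t-test. Two branches follow from that result.

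- **Significant:** "If there is a statistical significance, a regression model will be conducted to evaluate the effect of exercise intensity". For this model, "The fixed effect of time (baseline and postexercise), exercise intensity and study group will be included in the model".
- **Not significant:** "If no statistical difference is detected, repeated‐measures ANOVA will be performed to assess significant differences between both groups". Time is the within-subject factor, "with ‘group’ as a between‐subject factor". No intensity, session or period factor is named.

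The next sentence applies a Bonferroni correction for the number of comparisons, without saying which comparisons are counted. The Introduction gives the primary aim as the immediate effect of one exercise bout on central sensitization.

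**The concern.** Two things look wrong. First, a p-value selects the model. After a null intensity test, a second search for significance begins. After a positive one, the same effect is re-estimated by regression, so regression estimates exist only for outcomes already selected for significance and will tend to be too large.

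Second, the factor tested in the null branch is the order of the sessions. Both groups do both intensities, and the regression sentence itself lists intensity and study group as separate terms. A chance difference between the order groups could be read as a difference between exercise intensities, in exactly those outcomes where the proper comparison found none.

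**Working it through.** **1. The plan's own figure.** Section 2.8 gives 25.0 (SD 19.7) and 42.1 (SD 27.2), two-sided alpha 0.05 and power 0.80. Pooled SD = sqrt((19.7² + 27.2²)/2) = 23.75, and d = 17.1/23.75 = 0.720. The exact two-sample t-test needs 32 per arm (power 0.809; 31 gives 0.797), so 64 in total, and 64/(1 − 0.20) = 80. Both figures reproduce, and this point does not affect them. The plan states no figure for the fallback ANOVA.

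**2. What the ANOVA terms estimate.** Let the pre-to-post change be T after LOW and T + δ after HIGH, with no carryover. Period effects are common to both groups and drop out of every group comparison.

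- Summed change over both sessions: INV-A (T + δ) + T = 2T + δ; INV-B T + (T + δ) = 2T + δ. Difference 0. With sessions pooled and complete data, this is the group-by-time contrast.
- Mean of all four measurements: each group contains the same total, 2T + δ, above its baseline. Difference 0. This is the group term.
- Session 1 change minus session 2 change: INV-A δ; INV-B −δ. Difference 2δ. This is the crossover test of intensity.

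The cancellation is algebraic and needs no assumed SD.

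**3. Overlap with the carryover test.** That test compares participant sums between the same two groups. If all measurements are summed, it is the ANOVA group term. If changes are summed, it is group-by-time. If only postexercise values are summed, it is half the sum of the two contrasts. The same data contrast is thus read first as adequacy of washout and then as a difference between groups.

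**4. Simulated rejection rates.** N = 64, 6,000 runs per setting, each test at 0.05. Assumed, not from the protocol: between-subject SD 20, within-subject SD 12, mean pre-to-post change 5, no carryover, and intensity tested on change scores. Rates are unconditional on the first test.

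| Test | δ = 0 | 4 | 8 | 12 |
|---|---|---|---|---|
| Crossover t-test | 0.05 | 0.25 | 0.75 | 0.98 |
| ANOVA group | 0.05 | 0.05 | 0.05 | 0.04 |
| ANOVA group-by-time, two-level time, pooled | 0.05 | 0.05 | 0.05 | 0.05 |
| Group-by-time, four-level time | 0.05 | 0.30 | 0.88 | 0.999 |
| Group-by-time, session 1 only | 0.05 | 0.15 | 0.46 | 0.81 |

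At N = 80 the crossover test has power 0.31, 0.84 and 0.99 for effects of 4, 8 and 12, and the two pooled terms stay at about 0.05.

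**5. Chance of any intensity or group finding when none exists.** Three tests per outcome: the t-test, group, and group-by-time. The formula treats them as independent; the simulation uses 20,000 runs at N = 64.

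- No correction: 1 − 0.95³ = 0.143; simulated 0.141.
- Bonferroni on the two ANOVA terms only: 1 − 0.95 × 0.975² = 0.097; simulated 0.094.
- Bonferroni on all three: 1 − (1 − 0.05/3)³ = 0.049; simulated 0.048.

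**The case against.** The best defence has four parts.

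- **Bonferroni.** A reader might infer that the fallback inflates error to 14%. The document does not support that as a fixed figure: the correction follows directly, and if it covers all three tests the rate is about 5%. This stands. What remains is that its coverage is not stated.
- **The time term.** A reader might infer that the fallback only adds false-positive chances. It does not, because the time term addresses the stated primary aim, and pooling intensities after finding no difference between them is a recognisable staged approach. This also stands. But the term is a pre-to-post change without a non-exercise control, the stated purpose of the ANOVA is a difference between groups, and inference on the primary aim should not switch model according to another test's p-value.
- **Other readings of the factors.** A reader might infer that the ANOVA cannot test intensity under any reading. The two time levels are spelled out for the regression and not repeated for the ANOVA. With four levels, or with session 1 alone, group-by-time does carry intensity. Neither option is stated, however, and each would retest a hypothesis that was just not rejected; the session 1 version also discards half the crossover. If group was meant as HIGH or LOW, a between-subject factor contradicts the design.
- **The main comparison survives.** The HIGH-versus-LOW t-test runs in every case, and nothing says its result is withheld. This stands: the selection on significance affects the follow-up model, not that test.

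**Conclusion.** The concern holds in a bounded form. On the natural reading (group is the sequence, time has two levels, sessions are pooled), the fallback's group and group-by-time terms carry no information on intensity, and one of them essentially repeats the carryover test. No alternative reading makes the branch sound. The false-positive rate per outcome for intensity or group findings is undefined, at about 5%, 9% or 14% according to what Bonferroni covers.

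The absence of an intensity signal rests on the design alone, given no carryover. The power figures rest on assumed SDs, and the error rates on near-independence of the three tests. The documents do not support saying that the HIGH-versus-LOW comparison is lost, that the fallback is worthless, or that error is necessarily inflated. This is not detail left to an analysis plan: the article itself fixes the trigger, the model, the factors and the purpose.

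**What to change.** In section 2.9:

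1. Delete both branches that depend on the t-test's p-value.
2. For each outcome, run one pre-specified crossover analysis of HIGH versus LOW whatever its p-value, and report the estimate with a 95% CI. One suitable choice is a mixed model with intensity, period, sequence, session baseline and a participant random effect.
3. Estimate the pre-to-post change by intensity with a 95% CI, unconditionally, as the analysis of the primary aim, and note that there is no non-exercise control.
4. State that the sequence group term is not interpreted as an exercise effect.
5. State which comparisons the Bonferroni correction covers.

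The cost is rewording a few sentences before analysis. No further data or participants are needed, and the sample size is unchanged.

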##### Primary outcome measures

###### Exercise‐induced hypoalgesia

Exercise‐induced hypoalgesia will be assessed through pain pressure threshold (PPT) measurement, followed by a fatigue‐inducing exercise stimulus, and lastly, the same PPT measurements. The PPT will be measured using Echo Wireless Algometer (JTECH Medical, UT, USA). The PPT will be measured at two sites; (1) over the C5/C6 spinous process in the cervical spine; and (2) over the muscle belly of the left tibialis anterior. To ensure accurate measurement, an ‘x’ will be marked on the testing site with a marker during baseline assessment, and the same site will be used for postexercise PPT assessment. Pressure will be applied on the testing site at a rate of ∼5 N/s. Participants will be asked to state verbally when the sensation changes from ‘comfortable’ pressure to ‘unpleasant’ pain sensation. Triplicate reading, with a 30 s interstimulus interval, will be taken at each site, and the mean values will be used for analysis. The PPT measurements will be taken before and after the fatigue‐inducing exercise stimulus. The fatigue‐inducing exercise stimulus will be an isometric wall‐squat. Participants will be asked to maintain a wall‐squat position until fatigue or for a maximum of 3 min.

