###### Temporal summation

Temporal summation (TS) will be induced using a 256 mN punctate needle stimulator or ‘PinPrick’ (MRC Systems, Heidelberg, Germany) as the noxious stimuli, at two sites: (1) over the C5/C6 spinous process in the cervical spine; and (2) dorsal surface of the dominant hand between the second and third metacarpals. An ‘x’ will be marked at the testing site to ensure accuracy for baseline and postexercise assessment. In the test, a single stimulus will be applied initially, and participants will be instructed to rate the pain intensity verbally. Then after a period of 10 s, a series of 10 identical punctate stimuli will be applied at a frequency of 1 Hz, which has been shown to be sufficient to induce TS. The participant will state verbally the pain rating immediately following the last stimulus. A printed NPRS, labelled with digits from 0 to 10, with ‘0’ indicating ‘no pain’ and ‘10’ being ‘extremely painful’, will be displayed in front of the participant.

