### Sample size

2.8

For this clinical trial, the sample size is calculated based on PPT. Calculations for an appropriate sample size were performed with G*Power (v.3.1.9.6; Dusseldorf, Germany) (Faul et al., 2007). Given that there are no data on aerobic exercise testing with similar intervention groupings in chronic NP, the a priori power analysis was conducted based on data from an exercise intervention study with similar intervention grouping (Taimela et al., 2000). The sample size of this study is calculated based on the difference in mean PPTs (25.0 ± 19.7; 42.1 ± 27.2) between two different exercise interventions, a desired two‐tailed α = 0.05, β = 0.20, and an allocation ratio of 1:1. The calculations revealed that 64 participants would be sufficient. However, to allow a loss to follow‐up of 20% and taking a conservative approach, a total of 80 participants with chronic NP will be recruited.

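### Three primary measures share a Bonferroni rule with no stated family or divisor, and the sample size does not reflect it; one declared family of three tested by Holm would fix the error rate

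*Protocol article*

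**What the plan says.** Section 2.6.2 of the protocol article lists EIH, TS and CPM as primary outcome measures and does not rank them. For EIH, "The PPT will be measured at two sites", the neck and the left tibialis anterior. For TS, the pinprick is applied "as the noxious stimuli, at two sites", the neck and the dominant hand. For CPM, PPT is read over the tibialis anterior at 30, 60 and 90 s and at cold pain threshold. No site or reading is named as the tested variable.

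Section 2.9 compares HIGH with LOW by an unpaired t-test on within-subject differences between sessions. A significant result leads to a regression model, and a non-significant one to a repeated-measures ANOVA. Directly after the ANOVA comes "The significance level will be adjusted by the number of comparisons using Bonferroni correction". The next paragraph covers the lactate and central-sensitization regressions and ends with "Statistical significance is set at" P < 0.05.

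In section 2.8, "the sample size is calculated based on PPT", with "a desired two‐tailed α = 0.05, β = 0.20, and an allocation ratio of 1:1". The inputs are "the difference in mean PPTs (25.0 ± 19.7; 42.1 ± 27.2) between two different exercise interventions". The result is 64 participants, raised to 80 for 20% loss.

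**The concern.** The article chooses a multiplicity method, but the choice does not determine a threshold. Three tests is the count with one variable per measure. Five is the count with both EIH sites, both TS sites and one CPM summary. Eight is the count if the four CPM readings are tested separately. These give levels of 0.0167, 0.01 and 0.00625. If the Bonferroni sentence belongs only to the ANOVA it follows, the HIGH–LOW t-tests run at 0.05. A primary result at p = 0.02 would then be positive under one reading and negative under the other three.

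Two things are at stake. The chance of at least one false primary claim cannot be read from the plan. The divisor could also be settled once results are known, in a trial where section 2.5 says that neither assessor nor participants can be blinded. In addition, the level used for sizing is not the level that section 2.9 implies for testing.

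**Working it through.** **Inputs.** From section 2.8: means 25.0 and 42.1, SDs 19.7 and 27.2, two-sided 0.05, 80% power, 1:1 allocation, 20% loss. From section 2.6.2: two EIH sites, two TS sites, four CPM readings. Assumed, because the article gives no value: the within-subject correlation ρ of PPT between sessions (−0.2, 0 and 0.3 shown) and a correlation of 0.3 between outcomes.

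**1. Reproduce the plan's figure.** Difference = 42.1 − 25.0 = 17.1. SD = √[(19.7² + 27.2²)/2] = 23.75. d = 17.1/23.75 = 0.720. A two-sample t-test (noncentral t) needs 32 per group, 64 in total, with power 0.809. 64/0.80 = 80. The stated numbers are thus an independent-groups calculation at unadjusted 0.05.

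**2. Family-wise error if each test runs at 0.05.** For k independent tests it is 1 − 0.95^k.

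| k | Independent | Correlation 0.3 |
|---|---|---|
| 3 | 14.3% | 13.6–13.7% |
| 5 | 22.6% | 20.9% |
| 8 | 33.7% | about 30% |

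The last column is simulated. Some dependence is expected, since CPM takes its baseline PPT from the EIH assessment.

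**3. Power at 0.05/k on the plan's independent-groups basis.**

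| k | 32 per group | 40 per group |
|---|---|---|
| 2 | 0.719 | 0.823 |
| 3 | 0.663 | 0.778 |
| 5 | 0.590 | 0.718 |
| 8 | 0.524 | 0.659 |

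**4. Power for the contrast that section 2.9 actually tests.** Every participant does both intensities. SD_diff = √(19.7² + 27.2² − 2ρ × 19.7 × 27.2), which is 33.58 at ρ = 0. With N = 64 completers, equal sequences and 62 degrees of freedom, the noncentrality is 17.1 × √64/SD_diff. At ρ = 0 that is 17.1 × 8/33.58 = 4.07.

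| k | ρ = −0.2 | ρ = 0 | ρ = 0.3 |
|---|---|---|---|
| 3 | 0.895 | 0.943 | 0.990 |
| 5 | 0.855 | 0.917 | 0.983 |
| 8 | 0.812 | 0.888 | 0.974 |

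**5. Holm against Bonferroni, three tests, overall 0.05.** This is a simulation by normal approximation, with all three effects real and equal and outcome correlation 0.3. Figures are average power per outcome.

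| Effect strength | Bonferroni | Holm |
|---|---|---|
| As in the independent-groups calculation (noncentrality 2.88) | about 69% | about 77% |
| Crossover, ρ = 0 (noncentrality 4.07) | about 95% | about 98% |

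The normal approximation puts Bonferroni slightly above the exact 0.663 and 0.943 in steps 3 and 4.

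**The case against.** Five points can be made in the plan's favour.

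- **Power.** A reader might infer from step 3 that the 80% power is lost at any adjusted level. The documents do not support that. The trial is a crossover, and HIGH–LOW is tested within subjects. In step 4, PPT power stays above 80% at three, five and eight tests, even at an assumed ρ of −0.2. Even on the independent-groups basis, two tests with 40 per group give 0.823. This objection stands.
- **Two thresholds.** A reader might take the closing P < 0.05 as contradicting Bonferroni. It sits in the regression paragraph and can mean the level for those regressions, or the nominal level before adjustment. It is an ambiguity, not a contradiction.
- **A correction is promised.** The 14% applies only if the Bonferroni sentence is read as leaving out the t-tests. That is so, but its placement after the fallback ANOVA allows that reading. The counts of five and eight are also possible readings, not stated ones.
- **Condensed article.** The list of corrected comparisons is commonly left to an analysis plan, which is not shown. A missing divisor alone would be omitted detail. What remains is that the stated rule, its placement and the sizing level do not fit together, and that a better method exists for the same purpose.
- **Holm is a preference.** Bonferroni is valid, and on the crossover basis the gain for PPT is only about three percentage points. But Holm gives the same error control, is never less powerful and costs nothing. The gain is larger if effects are weaker, and the article gives no effect size for TS or CPM.

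**Conclusion.** The point holds as a defect in how the error rate is fixed, not as a shortfall in power. Three measures with several sites and readings are primary. The Bonferroni rule has no family or divisor and may not reach the HIGH–LOW t-tests. The sample size uses 0.05 for PPT only. Depending on the reading, the primary tests run anywhere from 0.05 to 0.00625, and three independent tests at 0.05 would give a family-wise error of about 14%.

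For PPT, the crossover contrast has about 94% power at 0.05/3 with 64 completers. That figure assumes a within-subject correlation of 0 and carries the cited study's means and SDs over to HIGH against LOW. Nothing comparable can be said for TS or CPM. The change should be made; it does not call the design into question.

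**What to change.** In section 2.9:

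- Declare one confirmatory family: the within-subject HIGH–LOW contrast for one named variable each of EIH, TS and CPM, three tests in all.
- Replace Bonferroni with Holm at overall two-sided 0.05. Order the three p-values and compare the smallest with 0.05/3, the next with 0.05/2 and the largest with 0.05, stopping at the first that fails.
- State that the other sites and readings are secondary, and that P < 0.05 applies to the secondary regressions.

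In section 2.8:

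- Say that 64 was computed for independent groups at unadjusted 0.05.
- Add power for the crossover contrast at the adjusted level, with the assumed within-subject correlation (about 94% at 0.05/3 for PPT with 64 completers and correlation 0).
- Say that no effect size is available for TS or CPM.

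The cost is wording in two sections and no added participants. The downside is that sites and readings not named lose primary status, so the three variables must be chosen before any comparison by intensity is seen.
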